## Abstract

**Background:**

Infertility produces infertility-related stress in both members of infertile couples, especially for infertile women. Some studies verified the negative relationship between infertility-related stress and outcomes of infertility treatments. Effective mental health care during fertility treatment is urgently needed, but there has been a lack of efficient support services. To reduce the infertility-related stress of infertile women, expressive art therapeutic schemes will be organized and implemented by certified international expressive art therapists.

**Methods:**

This study is a randomized controlled trial. Participants in the intervention group will receive expressive art therapies after the baseline investigation. Expressive art therapies will be led by the certified international expressive art therapist. The interventions include progressive muscle relaxation training, music meditation and drawing therapy. Participants in the control group will receive routine care. The Hospital Anxiety and Depression Scale (HADS) and Fertility Problem Inventory (FPI) will be used to investigate the anxiety, depression, and infertility-related stress of all participants at admission and at discharge.

**Discussion:**

This study will verify the effectiveness and efficiency of expressive art therapies for infertile women. The results will provide new knowledge on mental health care strategies for infertile women.

**Trial registration:**

ChiCTR, ChiCTR2300070618. Registered 14 April 2023.

**Supplementary Information:**

The online version contains supplementary material available at 10.1186/s13063-024-08324-1.

## Background

Infertility is defined as a failure in clinical pregnancy after 12 months of regular and unprotected sexual intercourse [1]. Infertile couples with no pregnancy history are classified as having primary infertility, while infertile couples with a pregnancy history are classified as having secondary infertility [2]. Globally, the incidence of infertility among couples ranges from 3 to 25% [3–5]. In China, the incidence of infertility ranges from 15 to 25% among couples of reproductive age [2, 6, 7]. The prevalence of infertility is increasing, which might be due to the trend toward delaying childbearing [4]. As reported, infertility is a public health issue that affects the mental health, marital satisfaction, and family relationships of patients [5]. Moreover, infertility affects more women than men in terms of psychological well-being and marital relationships [8]. Traditionally, not having children is often considered a woman’s fault. This prejudice makes many infertile women suffer discrimination in their lives and bear social consequences such as violence from family, marriage breakdown, or malicious evaluation from surrounding people. Due to the traditional culture of China, infertile women may have to endure more prejudice from family and society [9].

Infertile patients experience unique psychological stress, which is known as infertility-related stress. As reported, infertile women had higher levels of infertility-related stress than men [5]. Depression and anxiety represent distress-mediated symptoms of infertility [8]. As reported, different degrees of depression and anxiety affect 50% of infertile couples, affecting their quality of life [4]. In addition, depression and anxiety were related to decreased conception rates and lower outcomes of reproductive medicine, respectively [8]. Some studies also verified the negative relationship between infertility-related stress and outcomes of infertility treatments [10]. Therefore, the mental health of infertile women requires more attention, and effective mental health care during fertility treatment is urgently needed. Previous studies reported that infertile women coping with stress might benefit by disclosing their experience of infertility [11]. To improve quality of life among infertile women, mental care was suggested to encourage the expression and sharing of emotions during treatment [12].

Art plays a significant role in health promotion, and it is a method of healing. The arts are an essential part of health and nursing care because they are beneficial in disease prevention, cure, rehabilitation and care [13]. Expressive art therapy (EAT) has been incorporated into various programs as an element of both foundational and supportive treatment. EAT combines physical and psychological nonmainstream methods, including dance/movement, drawing, painting, sculpting, music, writing, sound, and improvisation [13]. EAT provides participants of all ages with a platform to release feelings, increase self-awareness, and explore hidden feelings in a supportive setting [14]. The participants do not need any experience or skills in art making, but the expressive art therapists need them. Considering cultural differences, expressive arts therapists should be culturally competent [15]. EAT has been applied in cancer patients, psychiatric patients, neurosurgical patients, pediatric patients, and domestic violence survivors [15, 16], but very few studies have explored the effectiveness of EAT in infertile women. As reported, releasing infertility-related stress is a way to promote the mental health of infertile women, which is essential to improve the outcomes of infertility treatments. Therefore, we designed a randomized controlled trial to verify the effectiveness of EAT in infertile women. We hypothesize that EAT will decrease the levels of infertility-related stress, depression and anxiety in infertile women.

## Methods

### Study design

This is a two-arm parallel randomized controlled trial led by an expressive art therapist. Infertile women who meet the inclusion criteria will be recruited. After providing written informed consent, participants will be assigned to either the control group or intervention group by using a random number table method. The allocation ratio is 1:1. The trial follows the Standard Protocol Items: Recommendations for Interventional Trials (SPIRIT). The schedule of enrolment, interventions, and assessments is presented in a SPIRIT figure (Fig. 1).

**Fig. 1 Fig1:**
[figure not shown]
Schedule of enrolment, interventions, and assessments, according to SPIRIT 2013

### Participants

Participants will be recruited from West China Second Hospital of Sichuan University, which is a women and children’s medical center in West China serving more than 5 provinces. Women are eligible if they (1) have been diagnosed with infertility, (2) will choose hysteroscopic surgery or/and laparoscopic surgery, and (3) have the ability to read and write in Chinese. Participants will be excluded if they have been diagnosed with mental illness. If participants from the intervention group and the control group are found to be sharing the same room, both will be excluded from the study to prevent any potential contamination.

### Intervention

Expressive art therapies will be led by the certified international expressive art therapist. The interventions include progressive muscle relaxation training, music meditation, and drawing therapy. The intervention time points include the first 24 h of admission (t_1_) and the first 24 h after surgery (t_2_). After baseline investigation (t_0_), participants in the intervention group will receive progressive muscle relaxation training (10 min), music meditation (10 min), and drawing therapy (40 min). The total duration of intervention is approximately 1 h. Participants in the intervention group and control group will receive general health education and routine nursing care. General health education and routine nursing care are standard practices in our hospital. By using them as the control group, we can establish a baseline for comparison, which makes it easier to evaluate the effectiveness of our intervention. Within the first 24 h after surgery, participants in the intervention group will perform progressive muscle relaxation and music meditation under guidance. At discharge (t_3_), participants in the two groups will complete the questionnaires. Participants are free to leave the study at any time for any reason without consequences. To improve adherence, all participants will be provided with guidance when they sign the informed consent form and commit to attending on the scheduled intervention time points.

### Measurement

A self-designed questionnaire will be used to collect sociodemographic information. The Hospital Anxiety and Depression Scale (HADS) is a self-reported screening questionnaire that detects mild anxiety and depression. It consists of 14 items, 7 items assessing anxiety (HADS-A), and 7 items assessing depression (HADS-D). Each item is scored on a 4-point Likert scale, ranging from 0 to 3, producing a sum score of 0 to 21 on each subscale. High scores indicate more severe symptoms [17]. The Mandarin version of the HADS was reliable and valid for the Chinese population. Cronbach’s *α* coefficients of the HADS-A and HADS-D subscales were 0.753 and 0.764, respectively [18, 19].

The Fertility Problem Inventory (FPI) was developed by Newton et al. in 1999 [20]. The FPI is a 46-item self-rating scale assessing the level of infertility-related stress. Each item is scored on a 6-point Likert scale, ranging from 1 to 6. The FPI includes 5 dimensions: social concern (10 items), relationship concern (10 items), need for parenthood (10 items), rejection of childfree lifestyle (8 items), and sexual concern (8 items). Global stress is calculated by summing five subscale scores. The total scores range from 46 to 276. Higher scores indicate higher infertility-related stress. The Mandarin version of the FPI (M-FPI) was reliable and valid for Chinese infertile couples. The test–retest reliability of the FPI was 0.83 (female), and Cronbach’s *α* coefficient was 0.927 [5, 21].

### Primary and secondary outcomes

The primary outcome is the level of infertility-related stress measured by the Fertility Problem Inventory (FPI), before participants are discharged from the hospital. The secondary outcomes are the levels of anxiety and depression measured by the Hospital Anxiety and Depression Scale (HADS) before participants are discharged from the hospital.

### Data collection and management

The Hospital Anxiety and Depression Scale (HADS) and Fertility Problem Inventory (FPI) will be used to investigate the anxiety, depression and infertility-related stress of all participants at admission (t_0_) and at discharge (t_3_) from the hospital. The questionnaire will be administered via Wenjuanxing, the most popular web-based survey platform in China. Completeness checks were performed by allowing submission only after mandatory answering of all questions. Participants scan the QR code to receive the questionnaire. The platform promised to keep all data strictly confidential. Only researchers on this team ([name] and [name]) will have access to the dataset. All the information will be coded without revealing personal data, and handled confidentially.

### Sample size

According to the pilot study, the standard deviations of FPI in the intervention group and control group were 22.91 and 29.01, respectively, and the means of FPI in the intervention group and control group were 144.29 and 159.31, respectively. We assumed that the number of patients in the intervention group was the same as that in the control group. The calculated sample size of 52 participants per group would provide 80% power with a two-tailed alpha error of 0.05. Estimating a dropout rate of approximately 5%, we will recruit at least 55 participants in each group.

### Randomization

The participants were assigned to the intervention group or control group by the random number table method. A computer-generated table of random numbers with parity matching was used. The obtained numbers were assigned to the continuously included participants. Participants with even numbers were assigned to the intervention group, and those with odd numbers were assigned to the control group. The generated random distribution sequence was placed in sequentially coded envelopes. After determining the eligibility of the participant, the researcher ([name]) opened the envelope and assigned the participant to the intervention group or control group.

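### Discharge FPI and HADS are compared by unadjusted t or rank sum tests although everyone has an admission score; adjusting for baseline would deal with the chance imbalance that odd/even allocation allows and raise power at almost no cost

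*Protocol article*

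**What the plan says.** Three parts of the protocol article matter here.

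- **Allocation.** Study design states "The allocation ratio is 1:1". Randomization adds "A computer-generated table of random numbers with parity matching was used", then "Participants with even numbers were assigned to the intervention group, and those with odd numbers were assigned to the control group". The sequence goes into numbered envelopes. No block size, cap or stratification factor is given, and the term for matching on parity is not explained.
- **Sample size.** Equal arms are assumed ("We assumed that the number of patients in the intervention group was the same as that in the control group"). From the pilot, "the standard deviations of FPI in the intervention group and control group were 22.91 and 29.01, respectively"; the matching pilot means are 144.29 and 159.31. The result is 52 per group for 80% power at two-sided 0.05, and after about 5% dropout "we will recruit at least 55 participants in each group". No overall total is stated.
- **Outcome and analysis.** The primary outcome is the FPI level before discharge, and the secondary outcomes are the HADS levels at the same point. Data collection and management has both scales completed by every participant at admission and again at discharge. Statistical methods compares the scores by t test or rank sum test, depending on normality. It names no covariate and gives the admission scores no role in the comparison.

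**The concern.** If each woman is allocated by the parity of an independent random number, nothing holds the arms equal in size or similar in starting level. That is acceptable when the analysis uses what is known about each woman's starting level. Here it does not. FPI is a trait-like questionnaire score, and Measurement cites a test–retest reliability of 0.83 in women, so admission FPI is the obvious predictor of discharge FPI. Comparing discharge scores alone leaves any chance difference at admission inside the treatment estimate. It also leaves the variance that admission scores explain inside the standard error. What is at stake is precision and a credible reading of a single trial of about 110 women. The validity of the test is not in question.

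**Working it through.** **Inputs.** From Sample size: means 144.29 and 159.31, so the difference is d = 15.02; SDs 22.91 and 29.01; two-sided alpha 0.05; 52 per group; 5% dropout. Pooled SD = √[(22.91² + 29.01²)/2] = √683.2 = 26.14. I take these SDs to apply to discharge scores; the article does not say so explicitly. The admission–discharge correlation r is not given and is assumed to be 0.3, 0.5 or 0.7.

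**1. The plan's own figure.** The normal approximation gives 48 per group and the exact t test 49 (power 80.4%). Dividing by 0.955, the efficiency of the rank sum test under normality, gives 49/0.955 = 51.3, so 52. The article does not say that this route was used. For a t test, 52 is slightly generous: noncentrality = 15.02/(26.14 × √(2/52)) = 15.02/5.13 = 2.93, power 82.7%. For dropout, 52/0.95 = 54.7, so 55, as stated.

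**2. What simple randomisation costs.** If exactly 110 women were enrolled (a total that the article does not state):

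- P(55/55) = C(110,55)/2¹¹⁰ = 7.6%.
- P(60/50 or more uneven) = 39%.
- Enrolling until both arms reach 55 takes 118 women on average (median 117), by simulation.

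Power with the pilot SDs, not assuming equal variances:

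| Intervention/control | Power |
|---|---|
| 55/55 | 84.7% |
| 60/50 | 83.6% |
| 50/60 | 85.2% |
| 65/45 | 81.8% |

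Averaged over all splits of 110, t-test power is 84.4%, against 84.8% at exactly 55/55. The loss is about 0.3 points.

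**3. What omitting the baseline costs.** With a linear baseline covariate, residual SD = 26.14 × √(1 − r²), df = 104 − 3 = 101, and noncentrality = 15.02/(residual SD × √(2/52)).

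| r (assumed) | Variance removed, r² | Residual SD | SE of difference | Power at 52 per group |
|---|---|---|---|---|
| no covariate | – | 26.14 | 5.13 | 82.7% |
| 0.3 | 9% | 24.93 | 4.89 | 86.0% |
| 0.5 | 25% | 22.64 | 4.44 | 91.8% |
| 0.7 | 51% | 18.67 | 3.66 | 98.2% |

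If r were 0, the lost degree of freedom would leave power at 82.7% to one decimal. At r = 0.5 the gain in precision equals that of an unadjusted trial with 52/0.75 = 69 per group.

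**4. Size of a typical chance imbalance.** If admission SDs are also about 26.14, the difference between arms in mean admission FPI has SD 26.14 × √(2/52) = 5.13. A difference of that size shifts the unadjusted discharge comparison by r × 5.13. That is 1.5, 2.6 or 3.6 points for r = 0.3, 0.5 or 0.7, or 10%, 17% or 24% of 15.02.

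**5. Unequal variances.** With the pilot SDs, the simulated type I error of the pooled t test is about 0.055 at 60/50, 0.060 at 65/45 and 0.04 at 45/65 (intervention/control). The unequal-variance test stays at 0.050.

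**The case against.** The strongest reply is that nothing here is invalid. Simple randomisation gives an unbiased comparison, chance imbalance is already counted in the standard error, and the unadjusted test has close to its nominal error rate. That stands, and it is why this is a point about efficiency. A second reply is that a condensed article may leave covariates to an analysis plan that is not shown. That would carry weight if the article were silent on the method, but it specifies the test, and the specified test ignores the admission scores.

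A reader might infer three stronger things that the document does not support.

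- **That the allocation fails its target because 55/55 occurs only 7.6% of the time.** The article sets a floor per group and no total of 110. An open sequence meets a floor by continuing, and an uneven split hardly affects power. The undefined matching on parity might even describe a balanced list.
- **That a fixed list of 55 and 55 labels is needed.** It is a preference. It makes late envelopes slightly more predictable in a trial where participants and most researchers know the allocation. It also has no replacements when women from opposite arms share a room and both are excluded. Recruitment began in June 2023, so the sequence may already be in use.
- **That the mix of operations biases the result**, because women are eligible if they "will choose hysteroscopic surgery or/and laparoscopic surgery". The article gives neither the mix nor any link between surgery type and FPI. Even assuming half have laparoscopy and a 10-point effect, surgery type would account for 0.5 × 0.5 × 10² = 25 of 683 variance units (3.7%). Its chance shift would have SD 10 × √(0.25 × 2/55) = 0.95 points, against a standard error of 4.98. That is ordinary sampling error.

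**Conclusion.** The point holds as a modest improvement to the analysis. Odd/even allocation, as described, is valid and costs little. The avoidable loss comes from comparing discharge scores without the admission scores that every woman provides. Adjustment would raise power at 52 per group from 82.7% to between 86% and 98% for correlations of 0.3 to 0.7, and would remove the part of the estimate due to chance baseline difference. The gain rests on the assumed correlation, on the pilot SDs applying at discharge, and on a roughly linear relation between admission and discharge scores. The cited reliability of 0.83 suggests that the correlation is not negligible. It is not an estimate of the correlation here, because surgery and the intervention fall between the two measurements. Robust standard errors are a smaller, free addition, and matter only if the arms turn out unequal.

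**What to change.** - **Primary comparison.** State that discharge FPI will be analysed by ANCOVA with treatment group and admission FPI as terms, reporting the adjusted mean difference with its 95% confidence interval. Analyse HADS-A and HADS-D in the same way, each with its own admission score.
- **Standard errors.** Use robust (unequal-variance) standard errors, and confirm that the named software version provides them.
- **Existing tests.** Keep the t or rank sum test as a supporting analysis, so that the normality check does not decide whether baseline is used.
- **Clarify the allocation.** Define the matching on parity, say whether the sequence is restricted, and say how 55 per group will be reached.
- **Optional.** Planned surgery type may be added as a second covariate, named in advance; the document does not show that it is prognostic. A fixed 55/55 list is likewise optional.

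The cost is one degree of freedom per model and a few sentences, with no extra participants, visits or questionnaires. The change should be dated and made before anyone compares outcomes by arm, including at the planned interim analysis.

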### Blinding

Medical staff will be blinded to group allocation. The researcher ([name]) who collected data will be blinded to group allocation. Other researchers and participants will be aware of the group allocation. The researcher who collected data will not be allowed to unblock the blinding.

### Statistical methods

The qualitative data (demographic characteristics) will be statistically described by number (*n*) and percentage (%) and statistically be inferred by chi-square test. The Shapiro–Wilk test will be used to assess the normality of our data. This test is suitable for small to medium-sized samples and will help us determine whether the data follows a normal distribution. The quantitative data (scores of HADS and FPI) will be described by mean/median and standard deviation (SD)/interquartile range (IQR) and be inferred by *t* test/rank sum test. In all analyses, a *P* value of < 0.05 indicates statistical significance. To handle protocol non-adherence in our randomized controlled trial, we will use an intention-to-treat (ITT) analysis. Additionally, we will conduct a per-protocol (PP) analysis to include only those participants who fully adhered to the study protocol. By comparing ITT and PP results, we aim to understand the impact of adherence on study outcomes. All instances of non-adherence will be documented and considered during data analysis and interpretation. SPSS 21.0 (SPSS Inc., Chicago, IL) will be used for statistical analysis.

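### FPI and HADS are measured at admission, but no baseline-adjusted treatment estimate is planned, so precision available at no cost is left unused

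*Protocol article*

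**What the plan says.** Under Data collection and management, both scales are used to assess anxiety, depression and "infertility-related stress of all participants at admission (t_0_) and at discharge (t_3_) from the hospital". Under Primary and secondary outcomes, the endpoints are discharge levels: "The primary outcome is the level of infertility-related stress measured by the Fertility Problem Inventory (FPI), before participants are discharged from the hospital", and "The secondary outcomes are the levels of anxiety and depression measured by the Hospital Anxiety and Depression Scale (HADS) before participants are discharged".

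Statistical methods says that HADS and FPI scores will be described by mean or median with SD or IQR "and be inferred by *t* test/rank sum test". A Shapiro–Wilk test is used to judge normality. The section does not attach a time point to the scores it will test. No covariate, regression model, mixed model or change score is mentioned anywhere in the article.

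The Sample size section works on the same footing, with two group means and two SDs and no baseline term: "the means of FPI in the intervention group and control group were 144.29 and 159.31, respectively", and "the standard deviations of FPI in the intervention group and control group were 22.91 and 29.01, respectively".

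**The concern.** A baseline measurement of the outcome is usually the strongest predictor of its follow-up value. Here both measurements use the same instrument within one hospital stay, so a moderate or high correlation is plausible. A two-sample test on discharge scores leaves the variation between women that was already present at admission in the error term. Adjusting for the admission score removes a share r² of the variance of the treatment estimate without adding a patient.

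Two things are at stake. One is the width of the reported interval, and the power if the true effect is smaller than the pilot difference. The other is the effect of chance imbalance: allocation is by parity of random numbers with no stratification described, so the arms may differ in admission FPI, and part of that difference carries into the unadjusted estimate. An adjustment chosen only after an imbalance has been seen is open to challenge; one specified in advance is not.

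**Working it through.** **Inputs from the protocol (Sample size).** Means 144.29 and 159.31; SDs 22.91 and 29.01; 52 per group; two-sided alpha 0.05; target power 80%; 5% dropout.

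- Difference: 159.31 − 144.29 = 15.02.
- Pooled SD: √[(22.91² + 29.01²)/2] = 26.14.
- Standardised difference: 15.02/26.14 = 0.575.

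**The plan's own figure.**

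- Normal approximation: n = 2 × [26.14 × (1.960 + 0.842)/15.02]² = 47.5, so 48 per group.
- Exact t test: 49 per group (power 79.6% at 48, 80.4% at 49).
- Rank-sum test, multiplying by π/3: 49 × 1.047 = 51.3, so 52 per group, as stated.
- Dropout: 52/0.95 = 54.7, so 55, as stated.

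At 52 per group the t test has 82.7% power. The planned size therefore meets its target without adjustment.

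**Assumed input.** The correlation r between admission and discharge FPI is not in the document. It is taken as 0.3, 0.5 and 0.7. The only related figure is "The test–retest reliability of the FPI was 0.83 (female"), under Measurement. That describes the instrument's stability on repeat administration. In this trial surgery, and in one arm the intervention, falls between the two measurements, so 0.83 is at most an optimistic upper guide.

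**Formulas.** Residual SD = 26.14 × √(1 − r²). Standard error = residual SD × √(2/52). Half-width = t quantile × standard error (1.9835 on 102 df unadjusted; 1.9837 on 101 df with one covariate). Power is from the noncentral t distribution with noncentrality 15.02/standard error.

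| Analysis | Residual SD | SE | 95% CI half-width | Power | Variance reduction |
|---|---|---|---|---|---|
| Unadjusted | 26.14 | 5.13 | 10.2 | 82.7% | – |
| ANCOVA, r=0.3 | 24.93 | 4.89 | 9.7 | 86.0% | 9% |
| ANCOVA, r=0.5 | 22.64 | 4.44 | 8.8 | 91.8% | 25% |
| ANCOVA, r=0.7 | 18.67 | 3.66 | 7.3 | 98.2% | 49% |

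The gain is modest at r=0.3 and substantial from r=0.5 upwards.

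**If the true effect is smaller than in the pilot.** For a true difference of 10 points (an assumption), the same calculation gives power of 49% unadjusted, 53% at r=0.3, 61% at r=0.5 and 77% at r=0.7.

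**Chance imbalance.** A baseline difference carries into the unadjusted estimate multiplied by r. If the baseline SD equals the pilot SD (assumed, since the article does not say when the pilot FPI was measured), a baseline difference at the 1.96-SE limit is 1.96 × 26.14 × √(2/52) = 10.05 points. The shift is then 0.3 × 10.05 = 3.0, 0.5 × 10.05 = 5.0, or 0.7 × 10.05 = 7.0 FPI points, against a planned effect of 15.02.

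**If change scores were intended.** Their variance is 2(1 − r) times the unadjusted variance: 1.4 times at r=0.3, equal at r=0.5 and 0.6 times at r=0.7. ANCOVA's factor, 1 − r², is 0.91, 0.75 and 0.51. Since 2(1 − r) − (1 − r²) = (1 − r)², a change score is never the more precise of the two.

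**The case against.** The plan is internally consistent: a discharge-level endpoint, a sample size for two means, and a two-group test. Under randomisation that comparison is valid and unbiased, and it meets its stated power. All of this stands, and it limits the point to precision.

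A second objection is that covariate adjustment is often left to an analysis plan that is not shown. That carries less weight here, because the article names the test for these scores. Moving to ANCOVA would replace a stated method and not merely fill in a detail.

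Three stronger readings are tempting, and the document does not support them.

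- A reader might infer that baseline scores enter no analysis at all. Statistical methods applies its tests to HADS and FPI scores without a time point, so describing or comparing baseline scores is not excluded. What can be said is that no baseline-adjusted treatment effect is stated.
- A reader might take 0.83 as the expected correlation and conclude that power would be near certainty. It is a property of the instrument, and the events between admission and discharge here could lower the correlation.
- A reader might say that any baseline imbalance passes in full into the result. Only r times it does, the 1.96-SE case is reached in about 5% of trials, and the unadjusted interval already allows for that variation. It is not an added bias.

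For HADS the article reports only Cronbach's alpha, which says nothing about the correlation between admission and discharge. A gain is likely in direction, but its size cannot be shown.

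**Conclusion.** The point holds as an improvement to a stated method, not as an error. Both scales are collected from all participants at admission, and the planned between-group inference makes no stated use of them. At 52 per arm, adjustment would raise power from 82.7% to between 86.0% and 98.2%, and narrow the half-width from 10.2 to between 9.7 and 7.3 FPI points, for r from 0.3 to 0.7. It would also remove a possible shift of about 3 to 7 points from a baseline imbalance at the 1.96-SE limit.

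These figures rest on the pilot means and SDs, an assumed r, a common residual variance although the pilot SDs differ, and, for the imbalance figure, a baseline SD equal to the pilot SD. That no adjusted estimate is stated is certain; how much would be gained is not.

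**What to change.** In Statistical methods, state that the primary analysis is a linear model (ANCOVA) of discharge FPI on randomised group with admission FPI as covariate, reporting the adjusted mean difference with its 95% CI. Specify the same model for HADS-A and HADS-D, each with its own admission score. Keep the unadjusted t test or rank-sum test as a sensitivity analysis. Fix this wording before outcome data are examined by group.

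The cost is analysis wording only. The admission scores are already collected, the web form accepts a questionnaire only when every item is answered, and SPSS fits the model. No extra participants, visits or questionnaires are needed, and the sample size can stay as it is.
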